### Randomisation and treatment allocation

#### Allocation concealment

The participating children with caries will first be categorised as either: (1) having a high caries rate (or severe early childhood caries, as defined by the American Academy of Paediatric Dentistry [1]), which is defined as the presence of more than 3 untreated caries surfaces, or (2) having a low caries rate. The children will then be allocated by a stratified randomisation method using a computer-generated random-number table into the following 2 groups:Group A – biannual topical application of 25 % AgNO_3_ solution followed by 5 % NaF varnish; andGroup B – biannual topical application of 38 % SDF solution followed by a placebo varnish.

#### Blinding

In this double-blind randomised clinical trial, the group allocation will be conducted by a dental assistant while the examiner will not know the allocation information. The examiner will not be informed of the treatment group allocation of the children and the children will not know the solution or varnish they receive throughout the study. The solution and varnish will be applied after the oral examination by another operator.

### Interventions

An independent operator will use a micro-brush to apply the appropriate solution and varnish according to the assigned treatment group after the oral examination. The Group A children will receive a 25 % AgNO_3_ solution (25 % silver nitrate, Gordon Labs, Carson, CA, USA) followed by a 5 % NaF varnish (Duraphat Varnish, Colgate-Palmolive, Endicott, NY, USA). The Group B children will receive a 38 % SDF solution (Saforide, Toyo Seiyaku Kasei Co., Osaka, Japan) followed by a placebo petroleum jelly varnish (Vaseline, Unilever, Englewood Cliffs, NJ, USA). The children in both groups will be instructed not to eat or drink for an hour after the application.

There is no adverse reaction of these two treatments, except the caries surfaces will become hard and black if the treatment has successfully arrested the caries lesions.

After the baseline examination, a report on the child’s oral health status will be provided to the parents with a note asking them to report to the study dentist if there are any side/adverse effects on the treated tooth and surrounding gum after treatment. During the follow-up treatments, the dentist will also look for related side/adverse effects, including blackening of the arrested caries surface, discoloured tooth, tooth hyper-mobility, and abscess formation.

### Follow-up evaluation

The follow-up oral examinations will be conducted every 6 months in the kindergarteners for 30 months by the same examiner using the same equipment, procedure, and diagnostic criteria as those used in the baseline examination. The oral hygiene and caries status of the child will be recorded. In addition, the presence of visible plaque and status of the included caries surfaces will be assessed. The examiner will not be the operator for the fluoride application.

### Outcome measure

The outcome measure (primary endpoint) is the number of soft (active) caries surfaces that become arrested (hardened) after 30 months. The outcome measure will be administered at baseline and at the 6-monthly follow-up examinations. Children and their parents have the right to receive dental treatment by other dentists. To our experience from previous clinical trials [11, 12], almost all participants will not be cared by other dental personnel, and we will include questions about the receipt of other dental treatment in baseline and follow-up interviews.

### Sample size and power calculation

This non-inferiority trial aims to measure the anti-caries efficacy of a 25 % AgNO_3_ solution followed by 5 % NaF varnish versus a 38 % SDF solution with a non-inferiority margin of −0.5 for the difference in mean number of arrested caries surfaces, which is considered clinically negligible (corresponding to an effect size = 0.25, assuming a standard deviation of 2.5 and true difference of 0) [11]. The estimated sample size, calculated with the help of a statistician, is based on the lower limit of the 2-sided 95 % confidence interval for the difference being set above the non-inferiority margin (−0.5), and statistical power of the study being set at 90 % (*β* = 0.10). The total required number of preschool children with caries will be 856 calculated with the use of statistical power analyses software, G*Power (version 3.1.7; Franz Faul, Universität Kiel, Kiel, Germany). Anticipating the caries prevalence to be 35 % [28] and the overall 30-month drop-out rate to be 20 % [11], the initial sample size for screening should thus be 3058 with a total of 1070 kindergarten children being recruited in the 2 study groups at the baseline examination.

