**Methods/Design:**

This study is a randomised, double-blinded, non-inferiority clinical trial. The hypothesis tested is that adjunctive application of 25 % AgNO_3_ followed by 5 % NaF is at least not appreciably worse than a 38 % SDF in arresting ECC. Approximately 3100 kindergarten children aged 3–4 years will be screened and at least 1070 children with caries will be recruited. This sample size is sufficient for an appropriate statistical analysis (power at 90 % (*β* = 0.10) with a 2-sided type-I error of *α* = 0.05), allowing for an overall 20 % drop-out rate. The children will be randomly allocated into 2 groups to treat their caries over a 30-month period:Group A – biannual adjunctive application of a 25 % AgNO_3_ solution and a 5 % NaF varnish, andGroup B – biannual adjunctive application of a 38 % SDF solution followed by a placebo varnish.

Clinical examinations will be conducted at 6-month intervals. Primary outcome measured is the number of active caries surfaces which are arrested. Information on confounding factors such as oral hygiene habits will be collected through a parental questionnaire.

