### Statistical methods

A data management and statistical analysis protocol has been developed for the clinical trial. This details the procedures for data entry, management and cleaning, and data analysis.

The collected data will be entered into an Excel file (Microsoft Corp., Redmond, WA, USA) by two persons, and the data will be compared to minimise data entry errors. The intra-examiner agreement in caries diagnoses will be assessed by Cohen’s Kappa statistics. The level of statistical significance for all 2-sided tests will be set at 0.05. For the 1-sided tests, the level of statistical significance will be set at 0.025.

An intention-to-treat analysis will be performed in this study. We expect that the drop-out rates of the two groups will be similar because the treatment protocols and treatment outcomes (arrested caries with blackening of the lesion) are the same. If the number of children who strayed from the protocol (for instance, by not adhering to the prescribed 6-month intervention, or by being withdrawn from active treatment) are different between the 2 groups, a per-protocol analysis will be performed. In that case, only the patients who complete the entire clinical trial according to the protocol will be counted towards the final results.

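### The stated margin, SD, effect size, confidence level and power do not give 856 children: 0.5/2.5 is 0.20, not 0.25, and at SD 2.5 the plan has about 83 % power, not 90 %

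*Protocol article*

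**What the plan says.** In the Protocol article, section Sample size and power calculation, the margin is −0.5 "for the difference in mean number of arrested caries surfaces, which is considered clinically negligible". The same sentence describes this as "corresponding to an effect size = 0.25, assuming a standard deviation of 2.5 and true difference of 0". The calculation rests on the lower limit of the 2-sided 95 % confidence interval "for the difference being set above the non-inferiority margin", with 90 % power. The result is: "The total required number of preschool children with caries will be 856". Allowing for 20 % drop-out and 35 % caries prevalence, this becomes 1070 recruited and 3058 screened.

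The significance level is given consistently elsewhere. The abstract (Methods/Design) states a 2-sided type I error of 0.05 with 90 % power and says of the recruitment target: "This sample size is sufficient for an appropriate statistical analysis". Statistical methods adds: "For the 1-sided tests, the level of statistical significance will be set at 0.025". The Discussion repeats the 2-sided 95 % interval and the 90 % power. Subject-level analysis gives the decision rule (lower confidence limit above −0.5) without naming the interval's level. One-sided 5 % and a 90 % interval are mentioned nowhere.

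**The concern.** Two things fail on a first reading. The effect size contradicts the margin and SD printed beside it. The sample size also looks too small for an effect size of 0.20 under a 2-sided 95 % interval, and too large for 0.25.

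This is the only confirmatory test in the trial, and the 90 % power figure appears in the abstract, the methods and the Discussion. If the SD of 2.5 is the planning value, the probability of failing to show non-inferiority when the treatments are truly equal is about 17 % rather than the stated 10 %. The recruitment and screening targets both build on 856, so they carry the same problem.

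**Working it through.** **Inputs** (all from Sample size and power calculation unless noted): margin 0.5; SD 2.5; true difference 0; 90 % power; 2-sided 95 % interval, that is one-sided α = 0.025 (also in Statistical methods); 856 evaluable children; 20 % drop-out; 35 % prevalence. The allocation ratio is not stated; I assume 1:1, so 428 per arm.

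**Effect size.** d = margin/SD = 0.5/2.5 = 0.20. To obtain 0.25, either SD = 0.5/0.25 = 2.0 or margin = 0.25 × 2.5 = 0.625. The article states neither.

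**Attempt to reproduce 856.** Normal approximation: n per arm = 2(z₁₋α + z₁₋β)²/d², with z = 1.960 (one-sided 0.025), 1.645 (one-sided 0.05) and 1.282 (90 % power). The last column uses the noncentral t distribution for a two-sample t test.

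| d | one-sided α | n per arm, unrounded | total, normal (rounded up per arm) | total, noncentral t |
|---|---|---|---|---|
| 0.20 | 0.025 | 2 × 10.507/0.04 = 525.4 | 1052 | 1054 |
| 0.25 | 0.025 | 2 × 10.507/0.0625 = 336.2 | 674 | 676 |
| 0.20 | 0.05 | 2 × 8.564/0.04 = 428.2 | 858 (unrounded 856.4) | 858 |
| 0.25 | 0.05 | 2 × 8.564/0.0625 = 274.0 | 550 | 550 |

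The stated inputs (first row) do not give 856; it falls about 19 % short of them (856/1052 = 0.81). Only d = 0.20 at one-sided 0.05 comes close, and 856 itself appears only when the normal approximation is rounded down. Using 80 % power instead (786–788 at d = 0.20 and one-sided 0.025), or inflating the t-test numbers for a rank test (898–993 at d = 0.20 and one-sided 0.05), does not return 856 either.

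The later steps do reproduce: 856/0.8 = 1070, and 1070/0.35 = 3057.1, rounded up to 3058. So 856 is not a misprint.

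**Power under the stated criterion** (one-sided 0.025, true difference 0). Normal approximation: power = Φ(d√(n/2) − 1.960).

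- 428 per arm, SD 2.5: 0.20 × √214 = 2.926; Φ(0.966) = 83.3 % (noncentral t 83.2 %).
- 428 per arm, SD 2.25: (0.5/2.25) × √214 = 3.251; Φ(1.291) = about 90 %.
- 428 per arm, SD 2.0: 0.25 × √214 = 3.657; Φ(1.697) = 95.5 % (noncentral t 95.5 %).
- 535 per arm (all 1070 analysed), SD 2.5: 0.20 × √267.5 = 3.271; Φ(1.311) = 90.5 % (noncentral t 90.5 %).

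For comparison, 428 per arm at SD 2.5 and one-sided 0.05 gives 89.9–90.0 %.

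**The case against.** A journal article condenses its protocol, and detail may sit in a full protocol or analysis plan. That does not help here: every input is printed, and the printed inputs disagree with one another.

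The stronger objections concern how far the conclusion reaches, and they largely stand.

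- **Cause.** A reader might infer that the calculation was definitely run at one-sided 5 %. The documents do not say so. The article names G*Power; a noncentral t calculation at d = 0.20 and one-sided 0.05 gives 429 per arm, total 858, because 428 per arm falls just short at 89.95 %. The explanation is likely but remains an inference.
- **True power.** A reader might take 83 % as the power of the trial outright. It depends on SD 2.5. The article's own effect size of 0.25 implies SD 2.0 at this margin, and then 856 would give 95.5 %. The study cited for the assumption is not available here, so the text alone cannot settle which figure is the slip. The near match of 856 to d = 0.20 favours SD 2.5 without proving it.
- **Type I error.** A reader might fear that the decision would later be taken on a 90 % interval to fit the sample size. Nothing suggests this: the level is fixed in Sample size and power calculation, Statistical methods and the Discussion. The defect concerns power; it neither biases the comparison nor raises the false-positive rate.
- **Recovery by adjustment.** One might hope that adjusting for baseline caries would make good the shortfall. The documents give no baseline–outcome correlation, so no such gain can be claimed.

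**Conclusion.** The point holds as an internal inconsistency. The effect size of 0.25 is incompatible with the margin and SD in its own sentence, and 856 follows from neither 0.20 nor 0.25 under the stated criterion. This conclusion does not depend on how 856 was obtained.

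The size of the consequence depends on the SD. At 2.5, with 1:1 allocation, true difference 0 and 20 % drop-out from 1070, power is about 83 % and the type II error about 17 %, some 1.7 times the stated 10 %. At that SD, 90 % is reached only if essentially all 1070 children are analysed, so the drop-out allowance is not really available. If the SD were about 2.25, the stated power would be right, and at 2.0 it would be understated.

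**What to change.** 1. In Sample size and power calculation, check the SD against the source of the assumption and state the margin, SD, effect size and one-sided alpha so that they agree.
2. If SD 2.5 is kept, change the effect size to 0.20 and restate power as about 83 % for 856 evaluable children (1070 recruited, 20 % drop-out). Make the same change to the power statement in the abstract and the Discussion. If another SD proves correct, state it and recompute.
3. Keep the 2-sided 95 % interval (one-sided 0.025) as the decision rule, and name that level in Subject-level analysis, where it is currently missing.

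These are wording changes; at SD 2.5 their only cost is a less favourable power figure. If the sponsor prefers to keep 90 % power at SD 2.5, the alternative is a larger target: 1052–1054 evaluable, which is 1315–1318 recruited (1052/0.8 = 1315; 1054/0.8 = 1317.5, rounded up) and about 3758–3766 screened at 35 % prevalence. Trial status reports recruitment as in progress, and the abstract gives 1070 as a minimum, so the article itself does not rule this out.

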### Statistical methods

A data management and statistical analysis protocol has been developed for the clinical trial. This details the procedures for data entry, management and cleaning, and data analysis.

The collected data will be entered into an Excel file (Microsoft Corp., Redmond, WA, USA) by two persons, and the data will be compared to minimise data entry errors. The intra-examiner agreement in caries diagnoses will be assessed by Cohen’s Kappa statistics. The level of statistical significance for all 2-sided tests will be set at 0.05. For the 1-sided tests, the level of statistical significance will be set at 0.025.

An intention-to-treat analysis will be performed in this study. We expect that the drop-out rates of the two groups will be similar because the treatment protocols and treatment outcomes (arrested caries with blackening of the lesion) are the same. If the number of children who strayed from the protocol (for instance, by not adhering to the prescribed 6-month intervention, or by being withdrawn from active treatment) are different between the 2 groups, a per-protocol analysis will be performed. In that case, only the patients who complete the entire clinical trial according to the protocol will be counted towards the final results.

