#### Subject-level analysis

Although the data for the primary outcome itself may not be normally distributed [11], making use of the central limit theorem with the relatively large sample size that will be recruited in this research, the distribution of the mean would be normal. Non-inferiority of the 25 % AgNO_3_ solution followed by 5 % NaF varnish to 38 % SDF solution can be claimed if the lower limit of the confidence interval for the difference in the mean number of arrested surfaces is greater than the non-inferiority margin of −0.5. This test for non-inferiority will only be performed for the primary endpoint, the number of arrested surfaces after 30 months. Furthermore, a Student’s *T* test will be performed to study the effects of the treatment on the number of arrested caries surfaces at the 18-month examination. This research will also study the effect modification. The variables that are considered to possibly modify the treatment effects on the outcome variable include the patient’s gender, baseline caries experiences, treatment group assignment, oral hygiene habits, fluoride agent use, parent-assisted tooth-brushing, dental visit behaviour, snacking habits, parental educational level, total family income, and family status (single-parent or two-parent households).

Besides the primary outcome, Student’s *T* tests will be also used to test the between-group differences regarding the number of new caries surfaces, increment in the number of non-vital teeth, and number of hyper-mobile teeth across the follow-up examinations.

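### As written, the month-30 non-inferiority comparison gains nothing from earlier counts on the roughly 214 expected drop-outs, and similar drop-out rates do not exclude bias

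*Protocol article*

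**What the plan says.** The primary endpoint (Outcome measure) is "the number of soft (active) caries surfaces that become arrested (hardened) after 30 months", and the same section adds that "The outcome measure will be administered at baseline and at the 6-monthly follow-up examinations". Follow-up evaluation confirms the schedule: "The follow-up oral examinations will be conducted every 6 months".

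Subject-level analysis allows a claim of non-inferiority "if the lower limit of the confidence interval for the difference in the mean number of arrested surfaces is greater than the non-inferiority margin", which is set at −0.5. It relies on the central limit theorem for normality of the mean and limits the decision to one time point: "This test for non-inferiority will only be performed for the primary endpoint, the number of arrested surfaces after 30 months". It names no model, baseline covariate, stratum term or earlier visit for this comparison. Randomisation, however, is stratified by high or low caries rate.

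On sample size (Sample size and power calculation), "The total required number of preschool children with caries will be 856". This is raised to 1070 for an expected 20% loss over 30 months.

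Statistical methods says "An intention-to-treat analysis will be performed in this study" and expects similar drop-out rates in the two groups, because treatment procedures and visible outcomes are the same. Its only explicit restriction to completers belongs to a conditional per-protocol analysis. It also refers to a separate statistical analysis protocol, which is not shown.

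**The concern.** A plain comparison of month-30 means uses only children who have a month-30 count. A child seen at 6, 12, 18 and 24 months and then lost adds nothing to it, although the child's earlier counts say a good deal about where the child was heading.

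Two things are at stake. The first is bias. The article's reassurance concerns drop-out rates. Equal rates leave the difference unbiased only if the children who leave differ from those who stay in the same way in both arms. The margin is half a surface, so a modest distortion matters. The second is precision: counts already collected, baseline active surfaces and the randomisation stratum could all narrow the interval at no cost in data.

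**Working it through.** **Inputs from the protocol article.** 856 children required, 20% drop-out, 1070 recruited, SD 2.5, margin −0.5, two-sided 95% interval (one-sided 0.025).

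**Assumptions, not in the article.** 1:1 allocation (535 per arm, 428 with a month-30 count). Correlation r of 0.6 to 0.8 between the last count before drop-out and the month-30 count. Where drop-out is selective, its log-odds rise by 0.5 for each SD by which the previous count is lower. Drop-out is 20% in each arm throughout.

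**Step 1, the plan's own figures.** 856 / (1 − 0.20) = 1070, and 1070 − 856 = 214 children expected without a month-30 count. The drop-out step reproduces exactly. The 856 does not follow from the stated 95% interval: margin 0.5, SD 2.5 and 90% power need 1052 at one-sided 0.025, while one-sided 0.05 gives 858. That is a separate matter, and 856 is taken as given here.

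**Step 2, precision of the plain comparison.** SE = 2.5 × √(4/856) = 0.171. Power at a true difference of 0 is Φ(0.5/0.171 − 1.96) = 83.3%.

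**Step 3, bias from selective drop-out.** At 20% drop-out and log-odds of 0.5 per SD, the mean previous count of those who stay is 0.096 SD above that of all children in the arm. The month-30 mean of those who stay shifts by b = 2.5 × r × 0.096, which is 0.144 at r = 0.6 and 0.192 at r = 0.8. With a true difference of −0.5, the false non-inferiority rate is 1 − Φ(1.96 − b/0.171), with b positive for selection in Group A and negative for Group B.

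| Selective drop-out in | r | Expected difference | Rate by formula | Rate by simulation |
|---|---|---|---|---|
| Group A only | 0.6 | −0.36 | 13% | 14% |
| Group A only | 0.8 | −0.31 | 20% | 21% |
| Both arms alike | 0.6–0.8 | about −0.50 | 2.5% | about 2.5–3% |
| Group B only | 0.6 | −0.64 | 0.25% | 0.2% |
| Group B only | 0.8 | −0.69 | 0.1% | 0.1% |

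With milder selection in Group A only (log-odds 0.25, r = 0.3 to 0.8) the rate is 4% to 8.5%.

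A cruder check needs no drop-out model. The bias is 0.20 × (treatment difference in completers minus treatment difference in drop-outs). For gaps of 0.25, 0.5 and 1.0 surfaces the bias is 0.05, 0.10 and 0.20. If it favours Group A, the error is 4.8%, 8.5% and 21.5%.

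**Step 4, using the earlier count.** In the Group A scenarios, a likelihood estimate that includes the previous count returns about −0.50 at both correlations. With random drop-out, and if every drop-out has one earlier visit, the variance ratio to the plain comparison is [(1 − r²)/0.8 + r²] × 0.8.

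- r = 0.6: 0.928, effective total 856/0.928 = 922, power about 86%.
- r = 0.8: 0.872, effective total 856/0.872 = 982, power about 88%.

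Simulated ratios were about 0.94 and 0.88. Any further gain from baseline active surfaces and the stratum is not counted here.

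**The case against.** The strongest objection is that the article fixes a decision rule, not an estimator. An interval for a difference in means can come from imputation or a repeated-measures model. Student's test is named for month 18 and the secondary outcomes, not for the month-30 interval. Missing-data handling is commonly left to an analysis plan, and the article says one exists. This stands in part: the absence of a missing-data rule is not a fault here. What remains is that the comparison the article does describe uses no earlier or baseline information, and that its stated reassurance about drop-out is insufficient.

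A reader might infer that the intention-to-treat label is false and that the analysis can only include completers. The text does not support this. Dividing by 0.8 is routine sizing under any analysis and does not define the analysis set. A reader might also infer that earlier visits are thrown away. They are not: the surface-level survival analysis and the 18-month test use some of them, although neither decides non-inferiority.

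Finally, the large error rates need selective loss in Group A only. Blinded children and matching procedures make arm-specific selection less plausible, though not impossible. This is a fair limit on the size claimed.

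**Conclusion.** The point holds as an improvement to the stated primary comparison. As described, that comparison gains nothing from the earlier counts of about 214 expected drop-outs, and similar drop-out rates do not establish absence of bias.

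The documents do not show that drop-out bias will enter the decision, or that it would favour Group A. Under the assumed mechanism the false non-inferiority rate is about 14–21%, about nominal, or below 0.5%, depending on where selection occurs. If children with more arrested surfaces were the ones to leave, the directions would reverse. The variance saving of 7–13% is an upper range, since some drop-outs may have no follow-up visit. The correlations and the drop-out model are assumptions; only the 20%, 856, 1070, SD and margin come from the article. The change is worth making, with medium confidence, because the unseen analysis protocol may already contain it.

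**What to change.** Take the month-30 difference and its two-sided 95% confidence interval from a repeated-measures model fitted by likelihood to all 6-, 12-, 18-, 24- and 30-month counts. Include arm-by-visit, caries stratum and baseline active surfaces as terms. Keep the −0.5 margin and the decision rule unchanged.

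Add a sensitivity analysis that progressively worsens the unobserved month-30 counts of Group A drop-outs until the conclusion changes. It should also account for randomised children with no follow-up visit, whom the model itself would leave out.

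If the separate analysis protocol already specifies an equivalent method, one sentence saying so is enough.

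The cost is analysis wording and modest programming, with no new data. The small downside is that the model assumes drop-out is explained by the counts observed before it. The sensitivity analysis examines how far the conclusion depends on that.

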## Methods/Design

### Trial design

This is a randomised, double-blind, non-inferiority clinical trial. The extension of the Consolidated Standards of Reporting Trials 2010 Statement will be followed [26]. The flowchart of this study is shown in Fig. 1.

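### The per-protocol analysis depends on an observed imbalance in deviations and then appears to supply the final result, which is the wrong rule for a non-inferiority trial

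*Protocol article*

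**What the plan says.** The Trial design section states: "This is a randomised, double-blind, non-inferiority clinical trial". Four statements in the Statistical methods section then settle which children are analysed.

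- The base analysis is unconditional: "An intention-to-treat analysis will be performed in this study".
- The authors expect balance: "We expect that the drop-out rates of the two groups will be similar".
- The per-protocol analysis is conditional. It opens with "If the number of children who strayed from the protocol", gives as examples of straying "by not adhering to the prescribed 6-month intervention, or by being withdrawn from active treatment", and ends with "are different between the 2 groups, a per-protocol analysis will be performed".
- The consequence follows: "In that case, only the patients who complete the entire clinical trial according to the protocol will be counted towards the final results".

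The decision rule under Subject-level analysis says that non-inferiority "can be claimed if the lower limit of the confidence interval for the difference in the mean number of arrested surfaces is greater than" the margin of -0.5. It names no analysis population, and no other section of the article mentions a per-protocol analysis. The Statistical methods rule is therefore all that determines which children support the claim.

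**The concern.** In a superiority trial, dilution from non-adherence works against the claim. In a non-inferiority trial it tends to work for it, which is why a per-protocol analysis is normally read beside ITT whatever the pattern of deviations. Here its use depends on imbalance, and both branches go the wrong way.

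- **Deviations similar in the two arms.** Only ITT need be run. Equal counts do not make deviation harmless: missed applications shared by both arms can move both means closer together, and that is the case in which the rule can leave the check out.
- **Deviations unequal.** Completers appear to become the final result. Exclusion after randomisation at different rates in the two arms is the setting in which the retained children are least likely to be comparable.

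The choice between the branches is read from post-randomisation data. At stake is the primary conclusion: it may rest on a diluted comparison with no check, or on a selected set that the data brought into play.

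**Working it through.** **Inputs from the article.** Sample size and power calculation: margin -0.5, SD 2.5, lower limit of a two-sided 95 % confidence interval (one-sided 0.025), 856 children required, 20 % drop-out, 1070 recruited. The allocation ratio is not stated; 1:1 is assumed, giving 1070/2 = 535 recruited and 856/2 = 428 retained per arm.

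**The plan's own step.** 856/(1 - 0.20) = 1070, so the inflation for drop-out reproduces, and 428 per arm is the number left after drop-out.

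**1. How often the literal trigger fires.** Let the deviation counts be two independent Binomial(535, p) variables with the same p, so that there is no true imbalance. The probability that they are unequal is 1 - Σ P(X = x)², which is close to 1 - 1/(2σ√π) with σ = √(535·p·(1 - p)).

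| True deviation rate in both arms (assumed) | σ | Probability that counts differ |
|---|---|---|
| 5 % | 5.04 | 94 % |
| 10 % | 6.94 | 96 % |
| 20 % | 9.25 | 97 % |

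A literal reading therefore makes the switch nearly automatic. Any looser reading turns it into a judgement about how large a difference counts.

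**2. What dilution can do if only ITT is run.** This branch matters only under a looser reading of the trigger. Let the fully adherent difference equal the margin, -0.5, and let non-adherence shrink it by a fraction c, so that the ITT difference is -0.5(1 - c).

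SE = 2.5 × √(2/428) = 0.171

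False non-inferiority rate = 1 - Φ(1.96 - 0.5c/SE)

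| Shrinkage c (assumed) | ITT difference | 428 per arm | 535 per arm |
|---|---|---|---|
| 0 | -0.500 | 2.5 % | 2.5 % |
| 5 % | -0.475 | 3.5 % | 3.6 % |
| 10 % | -0.450 | 4.8 % | 5.1 % |
| 20 % | -0.400 | 8.5 % | 9.6 % |

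The value of c is not the proportion of children who deviate. Suppose there are five half-yearly applications before the 30-month examination, with proportional loss of effect (both assumed). If 20 % of children miss one application, c = 0.20 × 1/5 = 0.04, and the rate is 1 - Φ(1.96 - 0.02/0.171), about 3.3 %. Missed single applications thus sit at the low end of the table.

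**3. Power in a per-protocol set.** With a true difference of 0, power = Φ(0.5/SE - 1.96).

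- 428 per arm: Φ(0.5/0.171 - 1.96) = 83 %.
- 374 per arm (70 % of 535): SE = 2.5 × √(2/374) = 0.183, power = 78 %.

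The 83 % is already below the planned 90 % on the stated SD and confidence interval. That shortfall belongs to the sample size calculation, not to the choice of analysis set.

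**The case against.** **ITT is not withdrawn.** ITT is promised without condition, and the last sentence can be read as merely defining the per-protocol set. That reading is possible. However, the sentence ties the final results to the triggered case and restricts them to completers, so replacement is the more natural reading. A reader might infer that the plan certainly discards ITT; the text does not go that far. What is certain is that the status of ITT after the trigger is left unclear.

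**The two branches cannot both be common.** This stands. If the trigger is literal, per-protocol would almost always run and the ITT-only branch would be rare. The dilution figures apply only under a looser reading.

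**Large dilution is not supported.** This also stands. A reader might infer error rates of 14 % or so by supposing that 30 % of the retained children contribute no treatment difference. Nothing in the article supports that. The 428 per arm already excludes drop-outs, a missed application is not the same as no treatment, and the Outcome measure section expects almost no care by other dental personnel and plans to ask about it. Dilution is also a tendency, and it depends on how missing 30-month outcomes are handled, which is not shown.

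**The separate analysis protocol may supply the detail.** The article says that one exists. A threshold for the trigger and the procedure for classifying deviations may be there, so their absence from the article is not the point made here. The conditional structure is stated in the article itself, and it is that structure which needs to change.

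**Conclusion.** The concern holds as a defect in a stated rule. Making the per-protocol analysis depend on unequal deviation leaves it optional where ITT tends to favour non-inferiority, and brings it in, apparently as the final result, where it is most exposed to selection bias. That conclusion needs no assumed non-adherence rate.

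The sizes are illustrative. The 94 to 97 % chance of a literal trigger assumes 535 per arm and equal true deviation rates of 5 to 20 %. The rise in false non-inferiority from 2.5 % to between about 3.5 and 8.5 % assumes 428 per arm, SD 2.5, a fully adherent difference exactly at the margin, and shrinkage of 5 to 20 %, with the low end the more plausible for missed single applications. No figure is offered for selection bias in the completers-only branch, because the article gives nothing from which to derive one.

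**What to change.** - In Statistical methods, delete the condition on unequal deviation counts and the sentence that follows it on whose data count.
- State that ITT (all randomised children, as randomised) and per-protocol analyses will always both be run and reported, with deviations defined and classified blind to arm before unblinding.
- In Subject-level analysis, state that ITT is retained as a final result and that the non-inferiority claim requires consistent conclusions in the two sets. One accepted form is a lower 95 % limit above -0.5 in both; another is to report both always and explain any discordance. Whichever is chosen should be fixed in advance.

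The cost is wording and one further run of the same analysis. If success is required in both sets, there is also a loss of power: the per-protocol set has about 83 % power at 428 per arm and 78 % at 374 (SD 2.5, one-sided 0.025, true difference 0). The overall chance of success can be no higher than the power in the smaller set.
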